### Randomization and allocation

Randomization is conducted by an independent investigator who is not involved in the recruitment, assessment, treatment, or data analysis. The randomization sequence is generated by computer-generated random numbers. Thirty-two eligible patients are randomly divided into VRMT group and RAVRMT group in a ratio of 1:1. The assignment of patients is concealed in an opaque, sealed envelope, and cases are numbered by an independent investigator in the order of entry into the group. Before starting an intervention, inform therapists of the patient’s specific number and intervention information in order to obtain the assigned treatment.

### Blinding

In this study, an assessor-blind method will be used. The assessor will evaluate the study results without knowing patients’ assignment, and conclusions will be drawn by a statistical analyst who is not involved in recruitment, screening, assessment, or intervention. In addition, the treatment process is performed independently by therapists who will not be involved in the procedures for information collection, assessment and data analysis. To minimize bias and interference, therapists do not provide patients with any information about the benefits and risks of treatment. The results of the assessment will be kept confidential to the researchers to ensure the objectivity of the assignment and the reliability of the study results. An independent staff will supervise the implementation of the blind method, and the blind code will be made public after completion of the statistical analysis. In the event of blinding failure, the patient will be excluded from the study protocol.

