### Sample size

The sample size was calculated based on the main efficacy indicator (FMA-UE score). We referred to a previous similar study as the basis for estimating the sample size [23]. The means and standard deviations (SDs) of FMA-UE scores in the two groups were 30.41 ± 9.07, 23.00 ± 5.58. The sample size estimation formula is as follows:$$ n=\frac{{\left({Z}_{\upalpha}+{Z}_{\beta}\right)}^2{\sigma}^2}{{\left({u}_r-{u}_c-\varDelta \right)}^2} $$

In this formula, *n* is the required number of each group; Assuming one-sided *α* = 0.025 and one-sided *β* = 0.1; The value of Δ is 10% of the mean of the control group in the previous similar study [24]; The required sample size is 13 in each group; Considering a 20% dropout rate, a total of 32 participants should be recruited (16 per group).

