### Assessment

The study period for each patient is 12 weeks. All patients will be assessed before and after a 4-week intervention for FMA-UE, MoCA, ADL, QOL, VAS, fMRI and safety measures. At week 8 after the end of 4-week intervention, all patients will be assessed their FMA-UE, MoCA, ADL, QOL, and VAS. All outcomes will be measured by assessors who have been uniformly trained, blinded to the randomization group after the baseline visit assessment.

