### Limitation

A double-blind design cannot be carried out in this study, which may cause deviations and affect the quality of the trial. However, we blind outcome assessors and statistical analysts to minimize the trial deviations.

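### Excluding a randomised patient when blinding fails can bias the comparison of arms, in either direction, and discards valid FMA-UE data

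*Protocol article*

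**What the plan says.** The Blinding section of the protocol article sets the design: "In this study, an assessor-blind method will be used". It also keeps the statistical analyst apart from recruitment, assessment and treatment, and has independent staff supervise the blinding. It ends with the rule at issue: "In the event of blinding failure, the patient will be excluded from the study protocol". The rule has no conditions, and neither the failure nor the exclusion is defined.

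The Limitation section confirms that patients are not blinded: "A double-blind design cannot be carried out in this study, which may cause deviations and affect the quality of the trial". The Assessment section refers to several uniformly trained assessors, "blinded to the randomization group after the baseline visit assessment". They rate FMA-UE after the 4-week intervention and again 8 weeks later. The Statistical analysis section names no analysis set that would keep the excluded patients.

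**The concern.** Because patients know their treatment, they are not the party whose blinding can fail. The trigger is that someone meant to be blind, in practice most likely an assessor, learns the arm. Assessors see patients at the visits where the primary outcome is measured, so the event falls after randomisation.

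It may differ by arm. Only RAVRMT patients have the affected limb attached to the device's traction end, so they have a distinctive experience to mention. It may also be related to response, because a patient who has improved or had discomfort has more reason to talk. Removing patients on such an event means that the groups compared are no longer the groups randomised.

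The rule also reaches further than its purpose. Unblinding compromises ratings made afterwards by the person who was unblinded. It does not invalidate the patient's earlier scores. A patient whose assessor is unblinded at the follow-up visit could lose a properly blinded post-treatment FMA-UE score.

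**Working it through.** **Inputs from the Sample size section.** "The means and standard deviations (SDs) of FMA-UE scores in the two groups were 30.41 ± 9.07, 23.00 ± 5.58". The difference is 30.41 − 23.00 = 7.41. "Assuming one-sided *α* = 0.025 and one-sided *β* = 0.1". The plan requires 13 per group and recruits 16 per group to allow for 20% dropout.

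**The plan's own figure.** The article does not say which SD entered its formula. With σ = 5.58 and Δ = 2.30 (10% of 23.00, an assumption because Δ cites a different reference), the printed formula gives (1.960 + 1.282)² × 5.58² / (7.41 − 2.30)² = 12.53, so 13. For dropout, 13 × 1.2 = 15.6, so 16. The allowance is therefore 16 − 13 = 3 per arm, and all of it is assigned to dropout. Any exclusion for blinding failure is an additional loss.

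**SD used below.** √[(9.07² + 5.58²)/2] = 7.53.

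**Shift when better responders are excluded.** Assumptions: no true effect, exclusions in RAVRMT only, outcome X in SD units standard normal, and probability of exclusion p(X) = 1/(1 + exp(−(a + cX))), with a set to give the stated exclusion rate. The mean of those kept is E[X(1 − p(X))]/(1 − rate), multiplied by 7.53.

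| Excluded from RAVRMT | c = 0.5 | c = 1.0 | Share of 7.41 |
|---|---|---|---|
| 5% | −0.19 | −0.35 | 3–5% |
| 10% | −0.37 | −0.68 | 5–9% |
| 20% | −0.72 | −1.30 | 10–18% |

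**Shift when poorer responders are excluded.** Simulation with no true effect, 16 per arm, 1 to 4 RAVRMT patients removed with weight exp(−c × response/SD), one-sided t test at 0.025, 8,000 runs per setting.

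| c | Spurious difference, 1 to 4 removed | One-sided type I error |
|---|---|---|
| 0 | about 0 | 0.023–0.025 |
| 0.5 | +0.24 to +1.02 | 0.034–0.058 |
| 1.0 | +0.39 to +1.74 | 0.037–0.092 |

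The two tables have opposite signs. The row c = 0 shows that exclusion unrelated to response causes no bias, only a smaller sample.

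**Power.** Two-sample t test, difference 7.41, SD 7.53, one-sided 0.025, noncentrality 7.41/[7.53 × √(1/n₁ + 1/n₂)].

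| RAVRMT / VRMT | Noncentrality | Power |
|---|---|---|
| 16 / 16 | 2.78 | 77% |
| 14 / 16 | 2.69 | 74% |
| 13 / 16 | 2.64 | 72% |

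If dropout has already brought both arms to 13, the same one-arm losses take power from 67% (13 / 13) to 63% (11 / 13) or 61% (10 / 13).

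**The case against.** The strongest defence is the wording. The sentence speaks of exclusion from the study protocol, not from the analysis. It might mean stopping protocol procedures or leaving a per-protocol set, and a statistical analysis plan that is not shown could define a full analysis set. This stands in part: the text is loose. But removal is the plain reading, nothing in the article limits it, and stopping participation would also lose later outcome data. A plan that analysed these patients as randomised would be at odds with the published sentence on that reading.

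A second objection is that the mechanism is conjecture. The documents do not say how blinding would fail. A clerical disclosure or a broken code would also count and need have nothing to do with response. This stands: bias is a risk and not an established fact.

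A reader might infer more than the documents support:

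- **That the rule does bias the trial, or favours one arm.** Neither is supported. Disclosure linked to marked improvement and disclosure linked to discomfort push in opposite directions.
- **That the effect is necessarily of the order of a point or more.** That needs about 20% exclusion in one arm, none in the other, and the stronger link to response. At 5% the shift is a few tenths of a point.
- **That power falls to 55–59%.** Those values come from 10 or 11 patients in both arms, which does not match exclusions in one arm only.
- **That the gap between 67% at 13 per arm and the planned 90% is due to this rule.** It belongs to the sample-size calculation, which is a separate matter.

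**Conclusion.** The point holds as a risk that the sentence itself creates. It prescribes an exclusion after randomisation, on an event that can depend on arm and response, and no passage keeps such patients in the analysis.

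The size is illustrative because no unblinding rate is given. Exclusion of 5–20% of one arm, with a moderate to strong link to outcome, moves that arm's mean by roughly 0.2 to 1.3 points in a direction that cannot be known beforehand. With no link to outcome there is no bias. The loss of precision is modest: 3 to 5 percentage points of power when 2 or 3 of 16 patients are lost from one arm. All of this rests on reading the sentence as removal from the study and its analysis.

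It should be corrected before follow-up begins, because the rule governs who contributes to the primary comparison and assessments not made under it cannot be recovered later.

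**What to change.** Replace the sentence in the Blinding section with:

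> If an assessor becomes unblinded, the event, arm, visit and cause are recorded by the independent staff supervising blinding; remaining assessments are done by another of the trained blinded assessors where possible; the patient stays in follow-up and in the primary analysis as randomised. A sensitivity analysis omits FMA-UE scores taken by an unblinded assessor.

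This also says what counts as a failure and what follows from it. The cost is a short replacement text and one sensitivity analysis. The article already provides for more than one trained assessor and for staff who oversee blinding, and the sample size does not change. The downside is small: a few unblinded ratings may enter the primary analysis, and the sensitivity analysis shows how much they matter.

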### Interventions

#### Groups

VRMT group: conventional therapy + VRMT;

RAVRMT group: conventional therapy + RAVRMT.

The interventions will be performed once a day for 4 weeks. VRMT and RAVRMT will be performed for 20 min per day. Follow-up will follow 12 weeks later.

#### Conventional therapy

All patients will receive conventional rehabilitation therapy provided by the Yueyang Hospital of Traditional Chinese Medicine and Western Medicine according to the results of rehabilitation assessment. Conventional rehabilitation therapy includes acupuncture, massage, physical factor therapy, exercise therapy such as posture and good limb position, joint stretch training, neurodevelopmental therapy (PNF technique, Bobath technique, Brunnstrom technique and Rood technique), active or passive limb training, etc. The conventional therapy received will be recorded but not influenced. At the same time, doctors will make basic medication plans according to the specific conditions of individual patients. We will track and record the type, frequency and dose of patients’ medication.

### Virtual reality mirror therapy

The VRMT group will receive VRMT using a clinically evaluated medical device (the RAVRMT robot). First, an occupational therapist with skilled operation explains the definition and content of VRMT to the patient. Second, the patient sits in front of the device, with a virtual reality head-mounted display on the patient’s head. Then, the unaffected hand holds the control handle to perform various motion trajectories in the game, which are transferred to the computer system and mirrored in real time on the virtual reality head-mounted display to show the various motion trajectories of the affected hand. Finally, the patient is required to carefully observe various dynamic simulation images of the affected hand through the virtual reality head-mounted display (Fig. 3).

**Fig. 3 Fig3:**
[figure not shown]
Schematic diagram of virtual reality mirror therapy

### Robot-assisted virtual reality mirror therapy

The RAVRMT group will receive RAVRMT using a clinically evaluated medical device (the RAVRMT robot). First, an occupational therapist with skilled operation explains the definition and content of RAVRMT to the patient. Second, the patient sits in front of the device, the affected upper limb is attached to the traction end of the device, the unaffected upper limb holds a control handle. Third, the unaffected hand holds the control handle to perform various motion trajectories, these trajectories are transferred to the computer system, and real-time simulations display on a virtual reality head-mounted display. Then, the traction end of the device guides the affected upper limb to perform these same motion trajectories, and real-time simulations display on the virtual reality head-mounted display. Finally, the unaffected hand holding the control handle and the affected upper limb guided by the traction end of the device move together to complete the game in virtual reality (Fig. 4).

**Fig. 4 Fig4:**
[figure not shown]
Schematic diagram of robot-assisted virtual reality mirror therapy. The patient’s left upper limb is on the affected side, and the right hand holds the control handle

### Follow up

To further explore the long-term effects of this trial, follow-up of patients after the 4-week intervention is required. All patients will participate in an 8-week unsupervised follow-up period immediately after the end of a 4-week intervention. At week 8 of the end of 4-week intervention, patients will undergo clinical assessments to assess their FMA-UE, etc.

### Assessment

The study period for each patient is 12 weeks. All patients will be assessed before and after a 4-week intervention for FMA-UE, MoCA, ADL, QOL, VAS, fMRI and safety measures. At week 8 after the end of 4-week intervention, all patients will be assessed their FMA-UE, MoCA, ADL, QOL, and VAS. All outcomes will be measured by assessors who have been uniformly trained, blinded to the randomization group after the baseline visit assessment.

### Primary outcome

The primary outcome of this study is the mean change in FMA-UE scores between and within the two groups before and after the intervention and follow-up. FMA-UE is widely used in the assessment of upper limb motor function and can reflect the level of upper limb motor function in stroke patients. The total score of the upper limb is 66 points, which is divided into three parts: shoulder–arm (36 points), wrist–hand (24 points), and coordination (6 points), and lower scores indicate worse upper limb movement function. The FMA-UE is often used as the gold standard to test the validity of other scales [9, 25]. FMA-UE has excellent reliability and validity and is sufficiently sensitive to clinical and research practice [20].

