### Inclusion criteria

The Inclusion criteria include the following: (1) Diagnosis of stroke by clinical assessment and neuroimaging as defined by the International Classification of Diseases (ICD-11); (2) Regardless of gender, age between 30 and 70; (3) Hemiplegic; (4) Primary stroke, stroke course of 1–6 months; (5) Primary school or above, with normal cognitive function (Montreal Cognitive Assessment (MoCA) score of 26 or above); (6) Sufficient audiovisual level to complete necessary research examinations and virtual reality mirror therapy; (7) Patient’s informed consent.

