### Statistical analysis

Blind the statistician. The clinical data will be analyzed by SPSS25.0 software. For the measurement data of the obtained data, the normality test is first performed. For the measurement data conforming to the normal distribution, it is expressed as the mean ± standard deviation (x ± s). The paired t test is performed before and after the two groups, and the comparison between the two groups is used Two-way repeated measures analysis of variance (2-way repeated measures ANOVA) test. The non-normally distributed measurement data before and after a group of self-comparison uses the Wilcoxon signed rank test, and comparison between the two groups uses the Mann-Whitney signed rank test. The significance level of the statistical test is set to α = 0.05, and the one-sided test is performed. A data monitoring committee will not be implemented because all participants will be treated and adverse events are expected to be low.

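### The primary outcome combines within-group and between-group FMA-UE change at two times and names no deciding contrast, so recovery common to both arms could be read as a positive result

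*Protocol article*

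**What the plan says.** Primary outcome (protocol article) gives a single definition: the "mean change in FMA-UE scores between and within the two groups before and after the intervention and follow-up". It therefore contains change within each arm and the difference between arms, with follow-up included.

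Statistical analysis sets out the tests for normally distributed data. Within arms, "The paired t test is performed before and after the two groups". Between arms, "the comparison between the two groups is used Two-way repeated measures analysis of variance". Non-normal data go to the Wilcoxon signed rank test within an arm and a Mann-Whitney test between arms. One level covers all of them: "The significance level of the statistical test is set to α = 0.05, and the one-sided test is performed". The section ranks neither the contrasts nor the times.

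Other sections bear on how this should be read:
- The abstract's Discussion and the main Discussion both ask whether RAVRMT improves the arm more than VRMT does.
- Sample size is built on the means of two groups: "The means and standard deviations (SDs) of FMA-UE scores in the two groups were 30.41 ± 9.07, 23.00 ± 5.58".
- Inclusion criteria require "Primary stroke, stroke course of 1–6 months", and Conventional therapy gives routine rehabilitation to every patient.
- Study design and Interventions (Groups) put follow-up at 12 weeks. Follow up and Assessment put it 8 weeks after the 4-week intervention ends.

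**The concern.** The trial asks a comparative question, and only a comparison of the randomised arms answers it. In the first months after stroke, with rehabilitation in both arms and an active control, FMA-UE can be expected to rise whether or not the robot component adds anything. A paired test within an arm detects that rise. It says nothing about RAVRMT against VRMT. The pattern of a significant change under RAVRMT and a non-significant one under VRMT is not evidence of a difference either.

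Because within-group change stands inside the primary outcome, a report could present a significant paired test as a primary finding and be consistent with the protocol's wording. With no deciding contrast or time fixed, that choice could also be made after the results are known.

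**Working it through.** **Inputs from the protocol.** Evaluable patients: 13 per arm (Sample size). Level of the tests: one-sided 0.05 (Statistical analysis). Sample size uses a different level, "Assuming one-sided *α* = 0.025 and one-sided *β* = 0.1". I use 0.05 below because it is the level stated for the tests.

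**Assumptions.** The protocol gives neither the expected common gain nor the SD of change. I take a gain m of 2, 3 or 4 points and an SD of change s of 5 or 8, the same in both arms, so the true difference between arms is zero.

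**Step 1: the plan's own figure.** The printed formula is n = (Zα + Zβ)²σ² / (u_r − u_c − Δ)². The difference is 30.41 − 23.00 = 7.41. For the margin, "The value of Δ is 10% of the mean of the control group", which is 2.30 if that mean is 23.00. The denominator is then (7.41 − 2.30)² = 5.11² = 26.11. With (1.960 + 1.282)² = 10.51 and σ = 5.58, the control SD, n = 10.51 × 31.14 / 26.11 = 12.53, which rounds up to 13. The σ actually used is not stated. What matters here is that the trial was sized on a between-group difference and not on change within an arm.

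**Step 2: paired test within an arm, arms identical.** With n = 13 the noncentrality is λ = m / (s/√13), and the test rejects when t exceeds 1.782 (12 degrees of freedom). For m = 3 and s = 5, λ = 3 / 1.387 = 2.16 and the noncentral t gives P = 0.653. The arms are independent, so the chance of significance in at least one is 1 − (1 − P)² = 1 − 0.347² = 0.88. The chance of significance in RAVRMT but not in VRMT is P(1 − P) = 0.653 × 0.347 = 0.23.

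| SD of change | Common gain | Given arm | At least one arm | RAVRMT only |
|---|---|---|---|---|
| 5 | 2 | 39% | 63% | 24% |
| 5 | 3 | 65% | 88% | 23% |
| 5 | 4 | 86% | 98% | 12% |
| 8 | 2 | 21% | 38% | 17% |
| 8 | 3 | 36% | 59% | 23% |
| 8 | 4 | 52% | 77% | 25% |

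A single between-group test at one time stays at 5% in every row, because the common gain cancels.

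**Step 3: between-group contrast at two times.** If the arms were compared separately at the end of the intervention and at follow-up, each at one-sided 0.05, and either could count, the false-positive rate would be 1 − P(neither rejects). With an assumed correlation between the two test statistics this is 8.0% (0.7) to 8.8% (0.5) from the bivariate normal. Simulated t tests with 13 per arm agree (8.1% and 8.8%). This does not apply to the group-by-time test of the repeated measures ANOVA, which is one test across the visits. It applies to the Mann-Whitney fallback or to post-hoc contrasts, if either is used at both times.

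**The case against.** The strongest reply is that the protocol nowhere says what makes the trial positive. Primary outcome lists what is measured, while the stated aim, the sample size and a separate between-group test all point to the comparison of arms. On that reading, within-group change is only description. Part of this stands. A reader might infer that a significant within-group p-value by itself satisfies the primary outcome, and the text does not support that. It supports only that such a result could be presented that way. The percentages in Step 2 are chances that a paired test detects recovery. They become false-positive rates for the trial only under a success rule that the protocol does not state.

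Two further inferences also go too far. One is that there are six primary tests. The paired test is described only as before against after, and its repetition at follow-up is not stated. The other is that having two time points inflates the planned between-group error. The normal-data analysis is one ANOVA, and its group-by-time test holds close to the nominal level: simulated under no difference with 13 per arm and three visits, it rejected in 4.9% of runs under compound symmetry and 6.0% under a moderately non-spherical pattern without correction.

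It can also be said that such detail belongs in an analysis plan that is not shown. That does not dispose of the point. The protocol does not leave the definition open: it states that within-group change is part of the primary outcome. An analysis plan that removed it would depart from the protocol.

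**Conclusion.** The point holds as a defect in a stated definition. Within-group change and follow-up are placed inside the primary outcome, tests within each arm are planned at one-sided 0.05, and neither a contrast nor a time is named as deciding, although the trial's question is between-group.

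If the arms were identical, a paired test would be significant in a given arm 39–86% of the time at an SD of change of 5, and 21–52% at an SD of 8. In at least one arm it would be 63–98% and 38–77%. These figures rest on 13 evaluable patients per arm and an assumed common gain of 2–4 points. The gain and both SDs are assumptions, and the conclusion does not depend on their exact values. The 8–9% for two separate between-group tests is conditional on such tests being used and is the lesser part of the point.

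**What to change.** In Primary outcome, name one contrast as the sole primary outcome: the RAVRMT minus VRMT difference in FMA-UE at one stated time. The end of the 4-week intervention is the natural choice. Adjustment for baseline FMA-UE, which is already collected, is preferable, but the defect is cured without it.

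In Statistical analysis, state that efficacy rests on that contrast alone, make the follow-up difference secondary, and report within-group changes as means with confidence intervals. The paired t and Wilcoxon tests should not serve as evidence of efficacy.

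Reconcile the follow-up time across Study design, Interventions (Groups), Follow up and Assessment, since the secondary contrast needs a single date.

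The cost is wording in these sections. No new data, visits or patients are needed. Trial status says that recruitment has not started, although Recruitment dates the study's start to June 2022. In either case the change should be made and dated before any outcome data are seen by arm.
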